## Abstract

**Introduction::**

Reduced bone mineral density and increased risk of falls are related with Alzheimer disease, and these increase likelihood of bone osteoporotic fractures causing serious complications such as disability, fear of falling, loss autonomy, decreased quality of life, and anticipated mortality in elderly patients. Gait and balance disturb are 2 factors to favor falls in elderly, and in patients with cognitive impairment, the risk of falls increases to double. Exercise and Mediterranean diet produce beneficial effects for aging, cognitive decline, and are widely recommended to reduce the effects of osteoporosis, fall risk, and related fragility fractures. The primary objective of this study is to evaluate the short and medium-term effects during 6 months, of a multicomponent physical exercise program with a Mediterranean diet on bone mineral density, fall risk, balance, and gait by a controlled clinical trial in patients with Alzheimer disease.

**Methods::**

The study is a 6-month, randomized controlled parallel-group, single-blinded clinical trial. Institutionalized patients with Alzheimer disease will be included. The intervention group will perform a multicomponent physical exercise program in reduced groups, with a frequency of 3 sessions per week, associated with a Mediterranean diet. This program includes strength, balance, and aerobic resistance exercises, and in the main part of the session, also ludic exercises to improve agility, coordination, and balance. The control group will receive usual care. The outcomes to assess are the change of physical functions, such as gait and balance, and the change of bone mineral density by calcaneal quantitative ultrasound, during the study follow-up at 1, 3, and 6 months. This clinical trial will generate more and new evidence on the effects of a multicomponent physical exercise program and Mediterranean diet in patients with Alzheimer disease on risk of falls and osteoporotic fractures, the relation of these with bone mineral density, gait and balance, and the correlations between them.

**Ethics and dissemination::**

This study protocol has been approved by the Ethics Committee of the University of Salamanca. The results will be published in peer-reviewed journals and disseminated in national and international conferences, to the participants and their families, and the general public through the associations of people with AD.

**Trial registration ID::**

ClínicalTrials.gov ID: NCT04439097.

## Introduction

1

Alzheimer disease (AD) is a neurodegenerative disease, the leading cause of dementia worldwide. AD is associated with the aging process,^[1,2]^ and is showing an increasing prevalence in occidental countries, such as other chronic diseases associated with increased life expectancy.^[3]^ If dementia prevalence data are maintained, from the 2015 data, there would be an approximate 300% increase by 2050, with around 130 million patients with dementia.^[4]^ According to an estimate by Alzheimer's Disease International, the global cost of the disease in 2015 amounted to 818 billion (USD$), a 35% more than in 2010, and is expected to increase to 2 trillion (USD$) by 2030.^[5]^

Cognitive impairment and frailty are related and share pathophysiological bases and some results such as falls, fractures, disability, even mortality,^[6,7]^ and both clinical processes also share low physical activity and gait disturbances.^[7]^ In the same way, bone fragility is a clinical comorbidity in AD,^[8]^ and low bone mineral density (BMD) occurs at twice the rate in AD patients as in healthy elderly adults.^[9]^ A long-term study, with a 3-year follow-up, suggested that there is a significant association between cognitive impairment and low BMD.^[8,10]^ It even showed that older women with reduced BMD are at a higher risk of cognitive decline, in accordance with Chang et al,^[11]^ who evidenced an increased risk of dementia in subjects with diagnosis of osteoporosis or osteoporotic fractures in Asian populations. In addition, it is known that low bone mass conditions weaken the skeleton and increase likelihood of bone fractures.^[12–14]^

Falls are directly related to bone fractures, causing significant complications such as increased risk of disability, decreased quality of life, fear of falling, loss of autonomy, and anticipated mortality in elderly patients.^[12–15]^

Changes during aging in sensor-motor and vestibular systems influence mobility and balance, increasing the risk of falls.^[16,17]^ This has also been demonstrated in AD patients, but this association is not well understood yet. Furthermore, it is known that patients over 65 with dementia have a 2-fold increased risk of falls, compared with no demented elderly.^[17–20]^

Cognitive deficit in elderly patients with AD is associated with gait and balance disorders,^[21–25]^ and influences executive functions, attention, and visuospatial perception and enhances the risk of falls.^[25–29]^ Yoon et al^[21]^ suggest that impairment in balance and mobility begins during the subjective cognitive decline stage, especially among the most vulnerable populations of women and APOEε4 carriers; therefore, we can consider that the impairment in balance and mobility could represent a predictive surrogate marker of cognitive decline.^[21]^

Gait alterations appear in 50% of AD patients 3 years after the diagnosis of AD, and among these, 33% lose their capacity to walk. The prevalence of gait and balance alterations ranges from 9% to 52% depending upon the tool of assessment.^[20,22,30]^

There are many tests used to assess gait and balance in elderly, cognitive deficit, or AD patients, Tinetti Performance Oriented Mobility Assessment (POMA-T), timed up and go test (TUG), 1-leg balance test (OLB), and functional reach test (FR) being among the most used.^[16,20,21,30–34]^ For this reason, they were selected for use in our study.

Physical activity and exercise have been shown that can delay the progress of AD in an effective cost and sustainable manner.^[35]^ Currently, we know that exercise achieves improvement in cognition of elderly with AD,^[35,36]^ and have other beneficial effects improving physical function, increasing autonomy, and quality of life in patients with dementia.^[3,30,31]^ The studies showed evidence with different factors such as type of exercise, frequency, intensity, time, and follow-up of the intervention, participants, etc.^[30,35]^ Besides, pharmaceutical treatments fail to address the cause of AD, and only a few symptomatic treatments are currently available, providing modest improvements to patients’ livelihood, and normally with side effects that may include nausea, dizziness, and weight loss.^[2,37,38]^ Exercise has shown even more positive results in terms of mortality from different diseases and chronic conditions than poly-pills for cardiovascular prevention.^[39]^

Exercise can contribute to mitigate cognitive decline and AD because among some of its effects are to improve cardiovascular health and increase muscle mass, reduce oxidative stress and inflammation, and stimulate hippocampal plasticity,^[2,40]^ also, taking into account the possible effect on the appearance or delay chronic diseases,^[2,41]^ and thus, improve their quality of life and significantly reducing the global burden of AD representing a main nonpharmacological lifestyle intervention.^[2,42,43]^

Along with exercise, diet is another major factor in maintaining a lifestyle that has been shown to have positive effects on the risk of dementia and cognitive impairment.^[44–46]^ The Mediterranean diet (MeDi) has shown as a promise dietary pattern in recent research, decreasing dementia risk, through altering cardiovascular risk factors and lower levels of neuropathology,^[44]^ and fracture risk through improving bone and muscle health status.^[47]^ In general, the literature support that MeDi is one of the best diet model to maintain health, with a lower incidence of frailty or disability in old age.^[48]^ The MeDi is predominantly plant-based, with a high intake of vegetables, fruits, nuts, and legumes, moderately high intake of fish, low intake of red meat, and includes extra virgin olive oil.^[49]^

The American College of Sports Medicine recommends 150 minutes of moderate or 75 minutes of vigorous physical activity per week, preferably divided into 3 to 5 sessions, and muscle-strengthening activities 2 or more days per week, with a recommendation of 3/2 ratio of aerobic and strength exercise per week.^[2,50,51]^

A multicomponent physical exercise program (MPEP) is possibly the best intervention option to obtain greater beneficial effects in older people.^[7,52–54]^

Strength training, resistance, and balance, combined or separately, have shown beneficial effects on several symptoms or factors associated with AD. So, we can consider exercise as a useful tool to improve functional capacities as mobility, gait, balance and strength, executive functions, and thus decrease falls.^[7,24,36,52–58]^ Moreover, we must consider that exercise or planned physical activity is a helpful plan for maintaining optimal bone health regulating bone metabolism,^[41,59,60]^ although its mechanism to improve bone health is not exactly clear yet. However, it has been accepted that increasing muscle mass and mechanical stress in bones results in increasing or preventing the loss of BMD.^[41,61,62]^ Evidence has shown that regular exercise with moderate intensity would decrease bone resorption and increase bone mass in both healthy and pathologic subjects.^[63]^

For the above reasons, a MPEP was designed in elderly people diagnosed with AD through a group intervention that will be described later. Group interventions have been shown to have high therapeutic potential.^[64,65]^

### General and specific objectives

1.1

The general objective of this MPEP associated with a MeDi is to decrease the risk of falls and fractures through the improvement of the bone health and physical functions of people with AD temporarily admitted to a Center for people with Alzheimer's Disease and other Dementias (Center-AD). Specific objectives include evaluating the effect and the changes of the MPEP and a MeDi on bone mass, physical functions, and their relationship to fall risk. Therefore, the aim of this study is to evaluate the short and medium-term effects, during 6 months, of a MPEP and MeDi on BMD, fall risk, balance, and gait by a randomized controlled clinical trial in patients with AD.

## Methods

2

### Study design

2.1

This study is a randomized, controlled, parallel-group, single-blinded clinical trial. The protocol of the clinical trial received approval from the Ethics Committee of University of Salamanca, and shall be carried out in accordance with the Declaration of Helsinki. The informed consent is written and accessible in Spanish with the approved protocol. The clinical trial was registered in ClínicalTrials.gov ID: NCT04439097.

The study protocol conforms to the SPIRIT 2013 Statement (Standard Protocol Recommendations for Interventional Trials),^[66]^ and the Clinical Trial conforms to the CONSORT 2010 Statement (Consolidated Standards of Reporting Trials).^[67]^

### Recruitment/enrollment and allocating

2.2

Patients who request for admission to the Center-AD, and who meet the initial selection criteria will be invited to participate in the study. Patients and their families will receive oral and written information by the physiotherapist of the Center-AD, who will apply the intervention, and, after signing the informed consent (by the patient or the legal guardian), the patients will be cited to make the baseline assessment with a multidisciplinary evaluator team. They will be randomized and assigned to the study groups. The patients in the intervention group will be admitted, and in the control group, they will be placed on a waiting list for admission once their participation in the study has ended. The randomization will be undertaken by the physiotherapist and an independent member of the Direction of the Center, with no other involvement in the trial, by using a computerized randomization system (randomized.com). Into our research line, the data obtained in a pilot study and a preliminary clinical trial have helped to improve the design of our current study. See the flowchart in Figure 1.

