#### Control group

2.6.2

Participants allocated to the control group will receive usual care and continue with their life normally, without participating in a standardized exercise program, and with the possibility to receive physical rehabilitation when needed. They will be instructed to maintain their current physical activity level, and will have to carry out the evaluations provided for in the study at 1, 3, and 6 months, with a periodic telephone contact. When the control patients are admitted to the Center-AD, they will have the opportunity to participate in the MPEP as well as the intervention group.

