### Strengths and limitations

3.1

We consider having some strengths points in our study. The design of this study has been based on the experience and results of previous pilot study and preliminary nonrandomized controlled clinical trial. The procedures will be carefully conducted by a multidisciplinary professional group highly qualified in the care and treatment of patients with AD. The novelty of our study is based on the fact that it is the first longitudinal clinical trial aimed at assessing the effects of a MPEP with a MeDi in short- and medium-term over 6 months on the bone health status and the risk of falls by correlating them with gait and balance disorders.

Some limitations of this study should be noted. General conclusions can only be drawn with caution and no conclusions about our intervention results should be drawn beyond institutionalized patients with AD, which suggests that they are more affected. Finding eligible elderly people with AD, who do not attend a center where they receive some type of intervention with physical exercise, is currently difficult, which makes intervention biases easily can appear. This can considerably increase drop-out rate during follow-up and the length of the recruitment period. Other studies should attempt to address strategies to increase the recruitment capacity of eligible patients for the control group, and to carry out experimental designs with 2 or more intervention arms.

In our future studies, in the same line of research, we also want to assess in greater depth the impact of diet combined with exercise on our outcome variables and analyze the influence of the nutritional status of patients with cognitive impairment, as well as their relationships with physical, cognitive, and bone health. And the study results will be released to the participating physicians, referring physicians, patients, and the general medical community.

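### Allocation decides admission to the Center-AD, so the trial estimates admission plus exercise plus diet in applicants for admission, not exercise and diet in institutionalized patients

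*Protocol article*

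**What the plan says.** All references are to the protocol article.

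- **Source of patients (section 2.2).** "Patients who request for admission to the Center-AD, and who meet the initial selection criteria will be invited to participate in the study".
- **Consequence of allocation (section 2.2).** "The patients in the intervention group will be admitted, and in the control group, they will be placed on a waiting list for admission". The sentence goes on to place the controls' admission after their participation is over.
- **Control arm (section 2.6.2).** Controls "will receive usual care and continue with their life normally, without participating in a standardized exercise program". Physical rehabilitation is possible when needed. They attend the assessments at 1, 3 and 6 months, "with a periodic telephone contact". Later, "When the control patients are admitted to the Center-AD, they will have the opportunity to participate in the MPEP".
- **Intervention (section 2.6.1).** Defined as the MPEP, three sessions a week for 6 months, plus the Mediterranean diet. Admission is not listed as a component.
- **Aim (section 1.1).** To evaluate the effects of the MPEP and the diet. The general objective in the same section concerns people with AD who are temporarily admitted to the Center-AD.
- **Falls analysis (section 2.9).** The relative risk is presented as measuring the association of falls with taking part in the MPEP. The same sentence compares the intervention group with the control group.
- **Population (Abstract, Methods).** "Institutionalized patients with Alzheimer disease will be included". In section 3.1: "no conclusions about our intervention results should be drawn beyond institutionalized patients with AD".
- **Limitations (section 3.1).** These cover generalisability, intervention bias in controls, recruitment and drop-out. The difference in setting between the arms is not mentioned.

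**The concern.** Randomisation here assigns two things at once: the exercise-and-diet program, and entry to a specialised dementia center. The text describes and interprets only the first. A difference in gait, balance, bone status or falls, in either direction, could come from the program, from admission, or from both.

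Two conclusions are at risk. The first is attribution. The Discussion looks ahead to adapting the protocols to other settings, including work at home, and that step assumes the effect belongs to the program and would survive without admission. The second is generalisation. The limitations direct the reader to institutionalized patients, but the people randomised are applicants, and the comparator arm is by design not in the Center-AD.

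**Working it through.** **1. Admission by arm during follow-up.**

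| | Intervention | Control |
|---|---|---|
| Admitted to the Center-AD (2.2) | all, by design | none until participation ends |
| MPEP (2.6.1, 2.6.2) | yes | no standardized program; offered after later admission |
| Study Mediterranean diet (2.6.1, 2.6.2) | yes | no; usual care |

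Let A be admission, M the MPEP with diet, and T allocation. By design A = M = T for every patient. A model with both A and M has two identical columns, so only the combined A + M contrast can be estimated. Adding covariates to the planned repeated-measures MANOVA does not help, because no patient has A without M or M without A. Blinding the evaluators (section 2.3) protects the ratings but leaves the contrast unchanged.

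**2. Claim against contrast.** The contrast is A + M versus neither. The aim (1.1), the definition of the intervention (2.6.1) and the description of the falls relative risk (2.9) name M, or the MPEP alone. Section 3.1 does not close the gap.

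**3. Population.** Section 2.2 randomises applicants. Allocation is 1:1 (section 2.8), so half of them stay outside the Center-AD during follow-up. The Abstract and section 3.1 (institutionalized) and section 1.1 (temporarily admitted) describe a state that only the intervention arm is shown to enter, and only after allocation.

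**4. Does the sample size depend on this?** Inputs from section 2.8: difference 1.5 POMA-T points, SD 2, two-sided alpha 0.05, beta 0.2, drop-out 33%.

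- n per arm = 2 × [SD × (1.960 + 0.842) / 1.5]², with SD = 2, = 27.9, rounded up to 28.
- With drop-out: 28 / (1 − 0.33) = 41.8, rounded up to 42 per arm, 84 in total.

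The plan's figure is reproduced. It refers to a difference between arms and does not change when that difference is given its correct name.

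**5. Possible size.** The document gives no effect of admission, so the shifts below are assumptions. The last column is the chance of p < 0.05 if the MPEP and diet did nothing and admission alone produced the shift b. It uses 28 completers per arm and a two-sided normal test.

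- Standard error = 2 × √(2/28) = 0.535.
- Chance = 1 − Φ(1.96 − b/0.535) + Φ(−1.96 − b/0.535).

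| Assumed shift b (points) | Share of 1.5 | Chance of p < 0.05 |
|---|---|---|
| 0 | 0% | 5% |
| 0.25 | 17% | 7.5% |
| 0.5 | 33% | 15.5% |
| 1.0 | 67% | 46.5% |

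The chances are the same for a shift in either direction. A harmful shift would mask a benefit of the program.

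**The case against.** The best defence is that the setting is not hidden. Section 2.2 states plainly who is admitted and who waits, section 1.1 refers to admitted people, and section 3.1 restricts generalisation. Randomisation is valid for what is actually delivered, and section 2.9 already computes the falls relative risk between arms. Most of this stands. It means that the comparison itself is sound and that the falls calculation needs a better description, not a new method. It does not answer the point, because disclosing the allocation rule is not the same as naming admission in the intervention, the aim or the limitations. The restriction in section 3.1 also points to a population that the control arm does not match.

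A reader might infer more than the document supports:

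- **That controls live at home.** No section says so. The document says they are on a waiting list and carry on with normal life under usual care. What is established is that they are outside the Center-AD.
- **That applicants live outside every institution.** This is not stated either. The mismatch is with admission to this Center.
- **That specific Center features drive the outcome.** The Center's routine care is not described. The Discussion says the multidisciplinary group eases monitoring of diagnosis, medication and diet, but does not confine this to one arm. Diet is in any case a declared component of the intervention.
- **That the trial is invalid or the sample size wrong.** Neither follows.
- **That recording of other therapies is missing.** An article may leave this to the full protocol, so it is not part of the point.

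**Conclusion.** The point holds in this form: admission to the Center-AD is completely confounded with the MPEP and Mediterranean diet, and the text neither names it in the intervention nor acknowledges it as a limitation while crediting the effect to the program. The label institutionalized does not describe the randomised population. The confounding is total by design, on the single assumption that sections 2.2 and 2.6.2 are carried out as written. How much admission contributes to any observed difference is unknown, as is its direction. The figures of 17% to 67% rest wholly on assumed shifts of 0.25 to 1.0 point. The randomised comparison of the whole package stands, and so does the total of 84.

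**What to change.** 1. Restate the aim in section 1.1 and the eventual conclusion as the effect of admission to the Center-AD with MPEP and Mediterranean diet, versus waiting-list usual care outside the Center-AD, in patients with AD applying for admission.
2. Correct the population wording in the Abstract (Methods), section 1.1 and section 3.1 so that it refers to applicants for admission.
3. In section 2.9, describe the falls relative risk by allocated arm instead of by participation in the MPEP. The calculation does not change.
4. Add to section 3.1 that the effect cannot be attributed to exercise or diet separately from admission.

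These are wording changes only. Design, sample size and analysis model are untouched. The price is a narrower claim: the trial could no longer be presented as showing what the MPEP and diet do by themselves.

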### Blinding

2.3

The multidisciplinary care team, with a neurologist, a neuropsychologist, and a physiotherapist, will perform all evaluations without knowing if the patients were enrolled and the group to which the patients have been assigned, and they will not have a relationship with the physiotherapist who applies the intervention. An independent researcher, who will not know the identification of the groups, will carry out the statistical analysis.

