### Exclusion criteria

2.5

Patients are excluded if they present the following exclusion criteria:

Other associated pathologies that do not allow physical exercise due to having severe functional disability or being insecure (neurological diseases, severe cardiorespiratory pathology, etc);Impossibility to carry out the evaluation tests;Falls and other incidents or adverse events with severe consequences that cause disability and/or that do not allow the intervention to continue;Attendance at the MPEP is less than 75% in the total of the sessions between assessments. (Criterion applied to each period between assessments). Adherence control by the physiotherapist;Not performing the MPEP sessions for 2 or more consecutive weeks;Participate in another intervention program outside of this study, especially an exercise program (important intervention bias for the control group).

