### Outcome variables

2.7

In the baseline assessment, all variables will be measured including the sociodemographic variables. Later, all outcome variables will be measured at 1, 3, and 6 months (Fig. 1) and will be codified by the physiotherapist who will conduct the intervention. A summary of outcome variables in summarized in Table 1.

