### Sample size calculation

2.8

The sample size calculation has been made based on the potential modification of the score of the POMA-T. For this, we have considered the results obtained in the previous pilot study with 9 patients in a 1-month follow-up, and the preliminary trial with 72 participants with a ratio of 3:1 to the intervention group and the control one during 6 months. In the pilot study, the POMA-T was modified by 1.7 points. Then, in the preliminary trial, we accepted to calculate the sample size, as statistically significant, with a difference greater than or equal to 1.7 points with a dropTout rate of 15%.

In our current study, the sample size has been estimated to conduct a randomized controlled clinical trial with a 1:1 ratio between the 2 groups. In this new calculation, considering the data from the pilot study and some of the available data from the preliminary trial, we have reduced the minimal detectable change in the POMA-T to 1.5 points, with a standard deviation of 2 points and we have increased the drop-out estimated rate during the study to 33% by the difficulty to avoid intervention biases in the control group fundamentally. Therefore, with this, and accepting an alpha risk of 0.05 and a beta risk of 0.2 in a 2-sided test, 84 subjects are necessary, 42 in each group. The sample size calculation was made with the software “GRANMO sample size and power calculator” (7.12 version).

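### The physiotherapist who informs families and delivers the intervention shares in the randomisation, so allocation concealment is not assured

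*Protocol article*

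**What the plan says.** Section 2.2 (Recruitment/enrollment and allocating) first gives one physiotherapist the task of informing families: "Patients and their families will receive oral and written information by the physiotherapist of the Center-AD, who will apply the intervention". Consent is signed after that. Then "the patients will be cited to make the baseline assessment with a multidisciplinary evaluator team. They will be randomized and assigned to the study groups". Patients allocated to the intervention are admitted to the Center, and control patients wait for admission until their participation ends.

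On who randomises, the section says "The randomization will be undertaken by the physiotherapist and an independent member of the Direction of the Center", and continues "with no other involvement in the trial, by using a computerized randomization system (randomized.com".

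Section 2.3 (Blinding) places another physiotherapist in the evaluator team. It says of the evaluators that "they will not have a relationship with the physiotherapist who applies the intervention". The allocation ratio is given in section 2.8 (Sample size calculation): "a randomized controlled clinical trial with a 1:1 ratio between the 2 groups".

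**The concern.** Concealment protects a trial when nobody in contact with a candidate before entry can know or influence that candidate's next assignment. Here a person with such contact is a named operator of the randomisation. If that person can see or foresee an assignment, the way information is given to a family, or the timing of a baseline appointment, can vary with it.

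The setting makes this more than a formality. Families have asked for admission, and allocation decides whether they get it now or later. The treating physiotherapist will run groups of 5 to 8 patients and must keep them safe, so has a professional interest in who joins. Section 3.1 says that eligible patients not already receiving exercise are hard to find.

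At stake is the comparability of the two arms on prognosis. A difference introduced at entry looks like a treatment effect, and a larger sample does not remove it.

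**Working it through.** **1. Who is the physiotherapist in the randomisation sentence?**

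- Section 2.2 introduces one physiotherapist before that sentence: the person who informs families and will apply the intervention. The natural reading is that this person shares in the randomisation.
- Section 2.3 describes another, an evaluator who must not know the group. Reading the sentence as meaning the evaluator would conflict with assessor blinding, but it is strained, because that person has not yet appeared in the text.
- The phrase about having no other involvement in the trial can describe only the member of the Direction, since the physiotherapist delivers the intervention. So one of the two operators is independent and the other is not.

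**2. What separates that person from upcoming assignments?**

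- Order of steps: information, consent, baseline assessment, randomisation. This protects if each assignment is generated only at the last step.
- Computerised system: this describes how assignments are produced, not who can see the next one.
- Independent co-operator: this adds an independent person but does not take knowledge away from the other.
- The article does not say how the two divide the task or who holds a sequence, if there is one.

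The text therefore permits both a concealed and an unconcealed procedure.

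**3. The plan's own figure.** Inputs from section 2.8: difference 1.5 points, SD 2, two-sided alpha 0.05, beta 0.2, ratio 1:1, dropout 33%.

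- n per group = 2 × (1.960 + 0.842)² × 2² / 1.5² = 27.9, rounded up to 28
- after dropout: 28 / (1 − 0.33) = 41.8, rounded up to 42 per group, 84 in total

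This reproduces the stated 84, with power 80.1% at 28 per group. The concern changes none of these figures.

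**4. Scale, by assumption only.** Let b be a between-arm difference in POMA-T change caused by selection, with no true treatment effect. The documents give no value for b.

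- SE = 2 × √(2/28) = 0.535
- two-sided error = 1 − Φ(1.96 − b/SE) + Φ(−1.96 − b/SE)

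| Assumed b (points) | b/SE | Error, 28 per arm | Error, 42 per arm |
|---|---|---|---|
| 0.25 | 0.47 | 7.5% | 8.8% |
| 0.5 | 0.94 | 15.5% | 20.9% |
| 0.75 | 1.40 | 28.9% | 40.5% |
| 1.0 | 1.87 | 46.5% | 63.0% |

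A shift of 0.5 points is one third of the 1.5-point target. With all 42 per arm analysed (SE = 2 × √(2/42) = 0.436), the error is larger, because a fixed bias weighs more as the standard error shrinks.

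**The case against.** A reader might infer that allocation in this trial is open. The article does not say so. It describes a joint task with an independent person, a computerised system, and randomisation after consent and baseline. If each assignment is produced only at that point, or if the independent member alone holds the sequence, concealment could be intact. This objection stands, and it limits the conclusion to concealment not being assured.

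Several other points also stand:

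- The article does not say that the physiotherapist recruits. It does not name who invites patients; it assigns only the giving of information.
- On the natural reading no stated safeguard is broken. The treating physiotherapist is never described as blinded, and the blinding of evaluators and analyst in section 2.3 is untouched.
- It would be too strong to say that analysis can do nothing. POMA-T is measured at the baseline assessment, before randomisation, and section 2.9 plans a model with covariates, so measured imbalance can be partly adjusted. Unmeasured selection cannot.
- The direction of any steering is unknown. Pressure to admit could bring needier patients into the intervention arm as easily as it could keep them out.
- The treating physiotherapist's later roles in section 2.5 ("Adherence control by the physiotherapist") and section 2.7 ("will be codified by the physiotherapist who will conduct the intervention") arise after allocation. They are separate matters and not evidence about concealment.

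One part of the defence does not succeed. A condensed article may leave the mechanics of concealment to the full protocol, so their absence alone would be no finding. But the sharing of the task by the person who informs and treats patients is stated, and that role assignment is what needs changing.

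**Conclusion.** The concern holds in a limited form. The protocol article gives the person who informs families before consent and delivers the intervention a share in the randomisation, and states nothing that keeps upcoming assignments from that person. Selection at enrolment cannot be excluded; neither has it been shown that it will occur.

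This rests on reading the physiotherapist in the randomisation sentence as the treating one, which is the natural reading. The size cannot be estimated from the document. The range of about 7.5% to 46.5% for the nominal 5% error reflects assumed shifts of 0.25 to 1.0 points, SD 2 and 28 completers per arm. It shows how sensitive a trial of this size is to such a bias, not what this trial will suffer.

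**What to change.** In section 2.2, strike the physiotherapist from the sentence on who undertakes the randomisation. The independent member of the Direction then runs the computerised randomisation alone, holds any sequence out of reach of both the treating and the evaluating physiotherapist, and releases each assignment only after eligibility, signed consent and the complete baseline assessment are recorded.

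Blocking is not needed for this change. If blocks are used, their sizes should vary and be unknown to the treating physiotherapist, who sees who is admitted and could otherwise predict assignments late in a block.

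The cost is one sentence and one reassigned task. The independent person is already named, no staff are added, and the sample size stays at 84.
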